### Power and Sample Size

The primary outcome of interest is engagement, measured through click-through rates, session duration, and to-do checklist completion rates across the 6 experimental arms. These metrics allow us to assess how different combinations of prompts and gamification elements affect user behavior. This will help us determine which strategies are most effective for sustaining participation in self-guided programs.

The study is designed to detect small to moderate effect sizes in engagement differences between intervention groups. Expected effect sizes range from Cohen f=0.1 (small) to f=0.25 (moderate). Our goal is to obtain a power of 80% (β=.20) and a significance level of .05 (α) to ensure adequate sensitivity in detecting meaningful differences between groups.

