### Primary and Secondary Outcomes

The primary outcome is engagement with behavioral prompts, defined as whether a user clicks on a specific tip, type of tip, or checklist item and is directed to the associated course component (refer to Table 3). This outcome reflects the initial behavioral response to a specific nudge. It serves as the basis for understanding which types of prompts are most effective at initiating action within the course. Secondary outcomes reflect broader patterns of use and progression through the course. These include (1) completion of main course components (eg, submitting a goal, completing the depression and anxiety test, completing course sessions, and engaging with other tools defined in Table 3); (2) click rate, defined as the proportion of tips and checklist items clicked; (3) session duration, or the total time spent on the platform; and (4) number of course sessions completed, including badge acquisitions and quiz completions.

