### Engagement Metrics: Operational Definitions

Engagement is defined as follows:

Click rate is defined as tips or checklist items that users click on.Tip interaction is considered “complete” when a user clicks on a tip and completes an exercise.Gamification metrics (eg, progress bar status, quiz completion, badge acquisition) will be recorded as binary variables (earned vs not earned).Session duration is calculated as the elapsed time (in seconds) between a user logging in and logging out of the platform.

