### Ethical Considerations

All data collection policies and procedures adhere to international privacy guidelines, including the General Data Protection Regulation, the US Health Insurance Portability and Accountability Act, where applicable, and the Declaration of Helsinki [104-107]. At registration, all members endorse a checkbox confirming that they consent to have their data used for research purposes and approve the platform’s privacy policy.

The platform does not collect personally identifiable information except a user’s email address, which is required for registration confirmation, retrieval of lost passwords, and two-factor authentication. Email addresses are encrypted and stored in a separate database.

This study is conducted on a self-guided resiliency course for displaced Ukrainian refugees, but it does not measure clinical outcomes. While participants are randomized into 6 intervention arms, the study is classified as an RCT, but it is not an RCT under medical research standards [108]. To clarify, this study adheres to principles of an RCT, where participants are randomly assigned to conditions, but does not fall under medical trial classification as it does not measure health outcomes. The CONSORT-SPI guidelines for social and psychological intervention trials will be followed [103].

The primary outcome variable being tested is course engagement, not wellness or symptom reduction. The study does not evaluate whether participant engagement with course tools improves mental health or reduces emotional stress related to forced displacement. Any potential clinical effects of engagement strategies tested in this study will require investigation in future research.

Since this study does not measure clinical outcomes, it does not fall under ClinicalTrials.gov or the WHO International Clinical Trials Registry Platform requirements. However, to ensure transparency, the trial was registered with Open Science Framework, a widely recognized registry for social science and behavioral health research.

As the study was based on deidentified user data and did not collect medical or clinical measures, it was deemed exempt from further review by Evolution Health’s Institutional Review Board. This exemption is per regulatory standards for minimal-risk research involving nonidentifiable behavioral data.

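### Two adjoining sections state different primary outcomes, and one of the listed primary metrics, checklist completion, does not exist in three of the six arms

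*Protocol article*

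**What the plan says.** Protocol article, Primary and Secondary Outcomes: this section gives as primary "engagement with behavioral prompts, defined as whether a user clicks on a specific tip, type of tip, or checklist item", followed by arrival at the linked course component. The secondary list includes "2) click rate, defined as the proportion of tips and checklist items clicked" and "3) session duration, or the total time spent on the platform".

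Protocol article, Power and Sample Size: the primary outcome is "engagement, measured through click-through rates, session duration, and to-do checklist completion rates across the 6 experimental arms". The error rates are given once for all of this: "Our goal is to obtain a power of 80% (β=.20) and a significance level of .05 (α".

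Protocol article, Sample Size Calculation for ANOVA: the sample size comes from a one-way ANOVA comparing engagement metrics, in the plural, over six arms. It assumes normal residuals and equal variances.

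Protocol article, Randomization: arms 1, 2 and 3 are listed without a to-do checklist. Arms 4, 5 and 6 have one. Arm 6 is listed with progress bars and a checklist, and no tips.

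Protocol article, Engagement Metrics: Operational Definitions: "Click rate is defined as tips or checklist items that users click on", and "Session duration is calculated as the elapsed time (in seconds) between a user logging in and logging out of the platform".

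**The concern.** The primary outcome decides what the trial can claim, what the .05 refers to and what the sample size is for. Here a reader of one section expects a yes/no click per user. A reader of the next expects three metrics, one of them a duration and one a completion rate. Session duration is primary in one place and secondary in the other, and so in substance is click rate. Checklist completion is primary in one place and is not named as a primary outcome in the other.

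Two things follow. First, the sample size is attached to metrics treated as continuous, while the outcomes section names a binary primary outcome for which no calculation is given. Second, one alpha of .05 stands beside three primary metrics. Nothing says whether they are combined, ranked, all required, or each sufficient.

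**Working it through.** **1. The two primary outcomes side by side**

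| Metric | Primary and Secondary Outcomes | Power and Sample Size |
|---|---|---|
| Click on a prompt, yes/no | Primary | Not named |
| Click rate / click-through rate | Secondary (2) | Primary |
| Session duration | Secondary (3) | Primary |
| To-do checklist completion | Not named as primary | Primary |

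No metric has the same status in both sections.

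**2. Which metrics can be observed in which arms** (from Randomization)

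| Metric | Arms 1-3 | Arms 4-5 | Arm 6 |
|---|---|---|---|
| Checklist completion | No | Yes | Yes |
| Tip click | Yes | Yes | No, as listed |
| Click on any displayed prompt | Yes (tips) | Yes (both) | Yes (checklist) |
| Session duration | Yes | Yes | Yes |

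A six-arm comparison of checklist completion has no data in 3 of 6 arms.

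**3. The plan's own sample size**

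Inputs: 6 arms, alpha .05, power 80%, Cohen f = 0.1 and 0.25. Method: noncentral F with λ = N·f² and 5 and N − 6 degrees of freedom.

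- f = 0.1: 215 per arm (1,290 in total). The article gives 86 (516).
- f = 0.25: 36 per arm (216 in total). The article gives 28 (168).

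The stated figures do not reproduce. That is a separate problem, and the present point does not depend on it. It matters here only because any restatement of power should start from a correct base.

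**4. Error rate if any listed metric could carry the claim at .05**

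For m independent tests, familywise error = 1 − (1 − .05)^m.

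- m = 2 (the two metrics that fit a six-arm comparison, click-through and session duration): 1 − .95² = .0975.
- m = 3 (adding checklist completion): 1 − .95³ = .1426.
- Upper bound for three tests under any dependence: 3 × .05 = .15.

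The metrics come from the same users, so independence is unlikely. The article gives no correlation between them, so a range is assumed. Simulation under no effect used three normal metrics, six arms, 100 per arm and 20,000 replicates:

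| Assumed correlation | Familywise error |
|---|---|
| .3 | .139 |
| .5 | .128 |
| .8 | .105 |

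The simulation treats all three metrics as present in all six arms, as the power section words it. Step 2 shows that this is not so for checklist completion.

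**5. Cost of keeping three primary metrics**

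At .05/3 = .0167 per metric and 80% power, f = 0.1 needs 274 per arm (1,644) and f = 0.25 needs 45 per arm (270). With the planned 100 per arm, power at f = 0.1 is 43% at alpha .05 and 27% at alpha .0167. At f = 0.25 it exceeds 99% at either level. These figures are for six-arm tests.

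**The case against.** The strongest reply is that the power section says engagement is measured through three metrics, not that each will be tested separately or that any one suffices. Combination, ordering and adjustment are commonly left to an analysis plan, and neither that plan nor the registry entry is shown. This stands against any claim that the error rate is in fact inflated. It does not remove the contradiction, because an unseen plan could agree with at most one of the two sections.

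A reader might infer three stronger things that the article does not support.

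- That the sponsor will run three tests and choose among the results. No section says so.
- That the ethics section adds a third rival definition. Its sentence, "The primary outcome variable being tested is course engagement, not wellness or symptom reduction", is a general label used to explain why no clinical outcome is measured. It defines no metric.
- That click rate is a proportion in one section and a count in another. The operational definition omits a denominator but still calls the quantity a rate. It is incomplete rather than contradictory.

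It is also fair to object to 14.3% as a headline figure. It needs independence, and it counts a six-arm checklist test that cannot be run. Without that test the independent figure is 9.75%.

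**Conclusion.** The point holds as a contradiction in the current text. Two sections name different primary outcomes, alpha and the sample size are attached to only one of them, and one of its three metrics is undefined in half of the arms. This rests on the wording alone and needs no assumption.

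The error-rate consequence is conditional on any listed metric being allowed to carry the claim at .05. It would then be about twice to nearly three times nominal: 9.75% for two independent tests, 14.3% for three, and about 10% to 14% for three with assumed correlations of .8 to .3. The article does not establish that condition.

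**What to change.** Reconcile Primary and Secondary Outcomes with Power and Sample Size on one primary outcome that every arm can show. The outcomes section already offers a candidate: whether each user clicks on any displayed prompt. This keeps the question in the Objective section. Arms show different sets of prompts, so the text should say that the outcome describes the response to the whole set shown in that arm. Then:

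- Tie the .05 alpha and the sample-size statement to that outcome. If it is binary, base the calculation on a binary outcome.
- Make session duration and checklist completion secondary in both sections, and compare checklist completion only among arms 4 to 6.
- Define click rate once, as the proportion in the outcomes section: prompts clicked over prompts displayed. The Data Collection section says that display and clicking of tips are logged. The same is needed for checklist items.
- If several metrics are to stay primary, state the multiplicity rule, such as .05 divided by the number of metrics, and restate the power on that basis.

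The cost is small: edits to the outcomes, power and operational-definition sections, a new sample-size statement, and an update of the registration before outcome data are examined. The metrics moved to secondary lose confirmatory status.

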#### Sample Size Calculation for ANOVA

Given that engagement metrics will be compared across 6 arms, a one-way ANOVA test was used to estimate the required sample size. For a small effect size (f=0.1), approximately 86 participants per arm (a total of 516 participants) are required. For a moderate effect size (f=0.25), approximately 28 participants per arm (a total of 168 participants) are required. These calculations assume normality of residuals and homogeneity of variance for ANOVA-based analysis. Chosen effect sizes are based on prior research in digital health engagement studies [94-96]. In our prior RCT [23,24], engagement data were analyzed using mixed-effect logistic regression, which does not rely on these assumptions.

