### Multiarm Trial Rationale

The six study arms were developed to explore the individual and combined effects of behavioral prompts grounded in behavioral economics, to identify which strategies most effectively enhance engagement in a digital resiliency program. Each arm includes a specific configuration of tips, checklists, or gamification elements intended to test distinct motivational mechanisms. This design enables comparative analysis across different engagement strategies while remaining operationally feasible. These components tested include (1) directive tips, grounded in the theory of implementation intentions, which provide straightforward, actionable guidance; (2) social proof tips, which leverage peer effects by referencing the behavior of others to encourage participation; (3) present bias tips, designed to counteract temporal discounting by emphasizing short-term benefits of engagement; (4) to-do checklists, which introduce structured goals and progress-tracking to increase adherence; and (5) gamification, which builds intrinsic motivation through visual indicators of advancement and progress feedback.

While a full factorial design could have explored all possible combinations of these interventions, the current 6-arm structure is a deliberate balance between conceptual rigor and practical feasibility. This structure enables comparative analysis across a diverse set of nudge combinations without creating an unmanageable number of trial arms. It was also informed by operational constraints and the need for meaningful data distribution across arms.

Our study design is also a foundational step toward developing a predictive analytics dataset. The behavioral engagement data collected through the six arms will be used to build baseline models that inform AI-driven personalization strategies. Future iterations of the course will be updated with tailored nudges based on user profiles, and new user data will be used to validate and refine the models. We chose the current design to generate sufficient diversity and volume in behavioral data to create a baseline for our long-term, adaptive research agenda.

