## Discussion

### Hypothesis

From our previous study, we anticipate higher engagement in arms that include the to-do checklist, particularly when combined with gamification (arm 6) or social proof tips (arm 5) (H1 and H2). Previously, these combinations demonstrated higher click-through and completion rates in earlier research. We expect similar trends in this trial, though results may vary based on population characteristics and platform context.

The study will also contribute to the development of AI models capable of predicting and optimizing user engagement, allowing for the customized delivery of to-do items and tips based on behavioral phenotypes (H2). These models will be trained using the behavioral data collected across study arms. Ultimately, this approach aims to enhance long-term adherence by tailoring interventions to individual patterns of use.

In our previous research on user engagement within the platform’s social network, we observed that engagement patterns followed power law distributions [88]. A follow-up study found that demographic and condition-specific characteristics did not predict social network engagement [89]. However, this study will help determine whether course engagement follows similar power law properties or if age and gender are predictive of engagement outcomes, particularly given the inclusion of session duration and behavioral phenotypes as new analytical factors (H3).

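### The trial is sized on a 5-df omnibus ANOVA, which cannot confirm the stated expectation that the checklist arms do better; a named contrast of arms 4-6 v 1-3 would match it.

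*Protocol article*

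**What the plan says.** All references are to the protocol article.

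- **Sample Size Calculation for ANOVA:** the basis of the sizing is described in these words: "Given that engagement metrics will be compared across 6 arms, a one-way ANOVA test was used to estimate the required sample size". It gives 86 users per arm (516) for f=0.1 and 28 per arm (168) for f=0.25, and adds: "These calculations assume normality of residuals and homogeneity of variance for ANOVA-based analysis".
- **Power and Sample Size:** effects from f=0.1 to f=0.25, 80% power, alpha .05. No pattern of arm means is given.
- **Hypothesis:** "we anticipate higher engagement in arms that include the to-do checklist", most of all in arm 6 (with gamification) and arm 5 (with social proof).
- **Multiarm Trial Rationale:** the arms exist "to identify which strategies most effectively enhance engagement".
- **Randomization:** arms 1-3 have tips and no checklist. Arms 4 and 5 repeat the tip content of arms 1 and 2 and add the checklist. Arm 6 is gamification plus checklist, with no tips listed.
- **Abstract (Methods):** between-arm comparison, and interaction testing of each component. **Sample Size for Repeated Measures:** GEE and 15% attrition.

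The target is 600 users, 100 per arm.

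**The concern.** The test that fixes the sample size and the hypothesis it should serve do not match. The omnibus F is non-directional and spreads its sensitivity over five dimensions of difference among six means. The stated expectation lies mainly along one of them, checklist arms against the rest. A significant F would leave open whether the checklist arms were higher, and would not say which component was responsible. The article gives no power for any comparison that answers either question.

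Two things are at stake. A true checklist advantage at the small end of the planned range may be missed more often than necessary. And a significant result would not by itself support the claim that the trial is meant to make.

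**Working it through.** **Inputs.** Six equal arms; n=100 per arm (N=600), or 85 per arm after 15% attrition (600 × 0.85 = 510); alpha .05; f=0.10. Assumptions: two-sided contrasts, SD=1, equal variances, and the patterns of arm means shown below, since the article states none.

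**1. The plan's own figures.** For the omnibus F, power = P(F′(5, N−6, λ) > F crit) with λ = N f². Solving for 80% power gives 215 per arm (1,290) at f=0.10 and 36 per arm (216) at f=0.25. The stated 86 and 28 do not reproduce: 516 users at f=0.10 give 37%, and 168 at f=0.25 give 68.5%. That is a separate error in the same section. Here it means that the stated n cannot be taken as evidence of 80% power.

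**2. Omnibus power at the planned size, f=0.10.**
- N=600: λ = 600 × 0.01 = 6.0, power 42.9%.
- N=510: λ = 5.1, power 36.6%.

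At N=600 the omnibus test reaches 80% only at f of about 0.147 or more.

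**3. Contrast power when the checklist is the only effect.** If arms 4-6 exceed arms 1-3 by δ, the SD of the six means is δ/2, so f=0.10 means δ=0.20 SD. Noncentral t with pooled error df (594) and noncentrality δ/SE:
- Arms 4-6 v 1-3: SE = √(2/(3n)) = √(2/300) = 0.0816; 0.20/0.0816 = 2.449; power 68.6%. With n=85: SE 0.0886, noncentrality 2.258, power 61.6%.
- Arms 4+5 v 1+2: SE = √(1/n) = 0.100; noncentrality 2.0; power 51.5%.
- A checklist arm v a non-checklist arm: SE = √(2/n) = 0.1414; noncentrality 1.414; power 29.2%.

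**4. Other patterns.** Each pattern is rescaled to f=0.10, so omnibus power stays at 42.9% (36.6% at 510). Worked example for 0,0,0,1,1.5,1.5: mean 0.667; SD of means √(5.5/6 − 0.444) = 0.687; scale 0.1/0.687 = 0.1455; difference (4/3) × 0.1455 = 0.194 SD.

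| Relative means, arms 1-6 | Arms 4-6 minus 1-3 (SD) | Power 4-6 v 1-3, N=600 (510) | Power 4+5 v 1+2, N=600 (510) |
|---|---|---|---|
| 0, 0, 0, 1, 1, 1 | 0.200 | 68.6% (61.6%) | 51.5% (45.2%) |
| 0, 0, 0, 1, 1.5, 1.5 | 0.194 | 66.0% (59.0%) | 44.3% (38.8%) |
| 0, 0, 0, 1, 2, 2 | 0.186 | 62.2% (55.3%) | 38.6% (33.7%) |
| 0, 0.5, 0.5, 1, 1.5, 1.5 | 0.181 | 60.0% (53.1%) | 43.9% (38.4%) |
| 0, 0.5, 1, 1, 1.5, 1.5 | 0.156 | 48.0% (42.1%) | 46.5% (40.7%) |
| 0, 0, 0, 0, 1, 1 | 0.141 | 40.9% (35.7%) | 18.5% (16.4%) |
| 0, 0, 0, 0, 0, 1 | 0.089 | 19.4% (17.2%) | 5.0% (5.0%) |

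In the first four rows every checklist arm lies above every other arm. In the fifth, tips alone bring arm 3 level with arm 4.

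**5. What the contrast would need.** At f=0.10 with checklist as the only effect, 80% power takes 132 per arm: 792 analysed, or 792/0.85 ≈ 932 recruited. At f=0.25 and 600 users, the omnibus and the 4-6 v 1-3 contrast both exceed 99% in the first four rows, so the choice affects power only near the small end of the range.

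**The case against.** The case against has five parts, and most of it limits the point.

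- **The article does not say that the arms will be compared only by an omnibus F.** A reader might infer this from the sizing section, but there the ANOVA is the sizing tool. The Abstract names between-arm comparison and interaction testing of each component, and GEE is planned for the repeated data. The contrasts and multiplicity rule may be in an analysis plan that is not shown, so their absence is no fault. What stands is that the sizing is tied to none of these analyses.
- **The hypothesis is not a plain checklist-v-no-checklist comparison.** It singles out arms 5 and 6. A main contrast of 4+5 v 1+2 would drop arm 6 and, in the graded patterns with arms 1-3 equal, has 39-44% power, no real gain on the omnibus 43%. This is why the main contrast should be 4-6 v 1-3.
- **Planned contrasts do not identify the best strategy with more power.** Present bias (3 v 2) and arm 6 v 4 compare 100 with 100. A 0.20 SD gap has 29% power unadjusted and 16% at the first Holm step of three (alpha .05/3).
- **Arms 4-6 v 1-3 is not a pure checklist effect.** Arm 6 lacks tips and adds gamification, and arm 3 has no checklist counterpart. This stands, and calls for a supporting contrast.
- **The primary outcome includes clicks on checklist items, which arms 1-3 cannot make.** On that outcome the contrast could be positive merely because more is clickable. This also stands. It governs the choice of outcome but does not remove the mismatch.

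**Conclusion.** The point holds in a limited form. The sizing test does not match the directional expectation, and a significant F would neither confirm it nor name a strategy. At f=0.10 and 600 users, naming the 4-6 v 1-3 contrast raises power from 43% to about 60-69% (from 37% to 53-62% at 510) when all checklist arms are raised above the others. The gain shrinks to 48% v 43% if tips alone bring arm 3 level with arm 4. The contrast has about the same power as the omnibus (41%) if only arms 5 and 6 differ, and loses clearly (19%) if only arm 6 does.

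A reader might infer that the contrast rescues the sample size. It does not: power stays below 80% at f=0.10 in every pattern shown.

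The figures assume a continuous outcome with equal variances, two-sided tests and one observation per user. A binary click outcome or repeated measures would change the absolute values, so they serve mainly to compare the tests.

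**What to change.** 1. Name the 1-df contrast of arms 4-6 v arms 1-3 as the main arm comparison, fitted in the planned model or GEE with all six arms included.
2. Run it on an outcome that every arm can register, such as completion of main course components, which is already a secondary outcome.
3. Report 4+5 v 1+2 as the supporting contrast that isolates the checklist, with its power of 38.6-51.5% at f=0.10 and 600 users (first four patterns).
4. List social proof (2+5 v 1+4), present bias (3 v 2) and arm 6 v 4 (as a package) as Holm-adjusted secondary contrasts, labelled as low-powered. Keep the omnibus F as secondary.
5. Restate power for the main contrast with the assumed arm means, and correct 86 and 28 per arm.

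**Cost.** No extra users and no change to the arms. It is more than rewording, because the outcome for the main comparison must be settled first. The downside is low power for patterns outside the contrast, such as an effect in arm 6 alone, for which the secondary omnibus test is the safeguard. Reaching 80% at f=0.10 would still need about 792 analysed users even in the most favourable pattern.

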### Randomization

Participants will be randomly assigned to one of the following six arms, as presented in Figure 2:

Arm 1 (baseline control): directive tips only and no to-do checklist.Arm 2: directive tips + social proof tips and no to-do checklist.Arm 3: directive tips + social proof tips + present bias tips and no to-do checklist.Arm 4: directive tips + to-do checklist.Arm 5: directive tips + social proof tips + to-do checklist.Arm 6: gamification (progress bars) + to-do checklist.

Participants will be randomly assigned to one of the six experimental arms using computer-generated randomization in a 1:1:1:1:1:1 ratio. Randomization will be conducted at the point of user registration, ensuring equal probability of assignment to any condition. No stratification or blocking will be used, as randomization is expected to produce comparable groups given the planned sample size. Randomization will be logged automatically by the system to ensure reproducibility and allocation integrity.

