#### Sample Size for Repeated Measures

Since engagement data will be collected across multiple time points, generalized estimating equations will be used to account for within-subject correlations. The generalized estimating equation is well-suited for analyzing longitudinal behavioral data in real-world digital environments, allowing more accurate estimation of SEs and robust modeling of repeated engagement behavior. A within-group correlation of ρ=0.3 was assumed, based on prior studies of engagement in digital health. This estimate aligns with findings from longitudinal analysis in behavioral health studies that report moderate within-person correlation of repeated engagement measures [101,102]. A 15% attrition rate was factored into the final sample size, suggesting an adjusted recruitment target of 100 participants per arm to maintain statistical power.

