#### Sample Size Justification

To ensure the predictive model has sufficient training data, the study aims to recruit a minimum of 600 participants (100 per arm). This sample size balances feasibility with analytic rigor, ensuring adequate power to detect differences in engagement and to train AI-driven predictive models. Refer to Multimedia Appendix 1 for the study’s CONSORT-SPI (Consolidated Standards of Reporting Trials-Social and Psychological Interventions) checklist [103].

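### The one-way ANOVA sample sizes do not follow from their stated inputs: f=0.1 needs 1,290 participants rather than 516, and f=0.25 needs 216 rather than 168

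*Protocol article*

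**What the plan says.** The section Power and Sample Size of the protocol article gives an expected effect range of Cohen f=0.1 to f=0.25 and sets the target: "Our goal is to obtain a power of 80% (β=.20) and a significance level of .05 (α".

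The section Sample Size Calculation for ANOVA names the method ("a one-way ANOVA test was used to estimate the required sample size") and gives two results: "For a small effect size (f=0.1), approximately 86 participants per arm (a total of 516 participants) are required" and "For a moderate effect size (f=0.25), approximately 28 participants per arm (a total of 168 participants) are required".

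The section Sample Size for Repeated Measures plans generalized estimating equations (GEE) with an assumed within-subject correlation of 0.3. It allows for 15% attrition, "suggesting an adjusted recruitment target of 100 participants per arm to maintain statistical power". The section Sample Size Justification then sets a minimum of 600 (100 per arm) and describes this as "ensuring adequate power to detect differences in engagement and to train AI-driven predictive models".

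**The concern.** Two features of the stated figures are suspect before any exact calculation.

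- **Size.** 86 per arm is very small for a five-degree-of-freedom omnibus test at f=0.1.
- **Ratio.** At fixed alpha, power and number of arms, the required total varies roughly as 1/f². Going from f=0.25 to f=0.1 should therefore multiply it by about (0.25/0.1)² = 6.25. The stated totals differ by 516/168 = 3.07, so they can hardly come from the same calculation.

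The recruitment target matters because the Results section keeps the experiment open until the sample size requirement is met. If that requirement is too low for the small effects the protocol says it expects, the six-arm comparison is more likely than not to miss an effect of that size under the stated test. A reader would meanwhile have been told that power is adequate.

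**Working it through.** **Inputs, all from the protocol article**

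- Test: one-way ANOVA (Sample Size Calculation for ANOVA: "a one-way ANOVA test was used to estimate the required sample size").
- Groups: k = 6 (same section: "Given that engagement metrics will be compared across 6 arms").
- Allocation: equal (Randomization: "using computer-generated randomization in a 1:1:1:1:1:1 ratio").
- Alpha .05, power 80%, f = 0.1 and 0.25 (Power and Sample Size).
- Planned total 600; 15% attrition leaves 600 × 0.85 = 510.

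**Formula.** For total N, the F statistic has df1 = k − 1 = 5, df2 = N − 6 and noncentrality λ = N·f². Power is the probability that this noncentral F exceeds the upper 5% point of the central F with the same degrees of freedom.

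**Step 1: the stated sizes**

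| f | Stated N | df2 | λ | Power |
|---|---|---|---|---|
| 0.1 | 516 | 510 | 516 × 0.01 = 5.16 | 0.370 |
| 0.25 | 168 | 162 | 168 × 0.0625 = 10.5 | 0.685 |

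Neither reaches 0.80.

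**Step 2: the sizes needed for 80%**

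| f | n per arm | N | λ | Power |
|---|---|---|---|---|
| 0.1 | 214 | 1,284 | 12.84 | 0.798 |
| 0.1 | 215 | 1,290 | 12.90 | 0.801 |
| 0.25 | 35 | 210 | 13.125 | 0.798 |
| 0.25 | 36 | 216 | 13.5 | 0.811 |

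The requirement is 215 per arm (1,290) and 36 per arm (216). The stated 516 is too small by a factor of 1,290/516 = 2.5, and 168 by 216/168 = 1.29. The ratio of the correct totals is 1,290/216 = 5.97, close to the expected 6.25.

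**Step 3: other routes to the stated figures**

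- Alpha .10 gives 175 and 29 per arm.
- Power 90% gives 276 and 45.
- Fewer groups raise the number per arm: k = 5 gives 240 and 40; k = 2 gives 394 and 64.
- A single-degree-of-freedom contrast gives 132 and 22.
- Averaging m repeated measures with correlation 0.3 multiplies the variance by (1 + 0.3(m − 1))/m. At m = 7 this is 2.8/7 = 0.40, and 1,290 × 0.40 = 516. The same factor turns 216 into about 86 in total, not 168. To reach 168 the factor would have to be 168/216 = 0.78. That lies between m = 1 (1.00) and m = 2 (0.65), so no whole number of measures gives it.

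None of these reproduces both figures.

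**Step 4: what 600 provides under the ANOVA described**

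| Analysed N | Power at f=0.1 | Power at f=0.25 | f with 80% power |
|---|---|---|---|
| 600 | 0.429 (λ = 6.0) | 0.999 | 0.147 |
| 510 | 0.366 (λ = 5.1) | 0.997 | 0.159 |

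**The case against.** The strongest objection is that the trial will not rest on a single-measure ANOVA. GEE on repeated engagement data is planned. If f=0.1 refers to a single measure, the correlation is 0.3 and the effect is constant over time, 600 participants would have about 63% power with 2 measures, 79% with 4 and 86% with 7 (79% with 7 after 15% loss). This stands as a limit on the conclusion. A reader might infer that the trial's planned analysis has only 43% power at f=0.1. The document does not establish that, because 43% belongs to the one-way ANOVA without attrition. Equally, the document gives no number of time points and so no basis for claiming the higher values. Nor does the objection rescue the published sizes, which are attributed to the ANOVA and fit no single number of measures.

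A reader might also infer that the protocol promises 80% power for small effects with 600 participants. It does not say so. The 80% is worded as a goal, and the two later sections mention neither 80% nor a small effect. Their statements are also true for part of the range, since 600 is ample at f=0.25, and 600 is a minimum rather than a cap.

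The attrition step might look short as well, since 86/0.85 = 101.2 and 100 recruited leaves 85. That is one person per arm against an approximate figure (power 0.366 rather than 0.370), and nothing should be made of it.

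Finally, pooling the checklist arms (4 to 6) against the others might look like a free way to recover power. It is not a sound remedy here. The two sets also differ in tips and gamification, checklist clicks count towards the primary outcome although arms 1 to 3 have no checklist, and the gain assumes that all between-arm variation lies on that one contrast.

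**Conclusion.** The sample sizes in Sample Size Calculation for ANOVA are wrong as written. With six equal arms, alpha .05 and 80% power, f=0.1 requires 1,290 participants, 2.5 times the stated 516, and f=0.25 requires 216 rather than 168. Under that ANOVA the minimum of 600 falls short of the protocol's own 80% goal at the lower end of its effect range. It meets the goal from f of about 0.15 upwards, or about 0.16 if 15% are lost.

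The correction of the two figures needs no assumption beyond the protocol's stated inputs. The power values for 600 and 510 assume one measure per participant and the normality and equal variances that the protocol itself states. They do not describe the GEE. They also do not settle whether Cohen f suits a primary outcome defined as clicking or not clicking, which is a separate matter.

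**What to change.** 1. In Sample Size Calculation for ANOVA, replace 86 per arm (516) with 215 per arm (1,290) for f=0.1, and 28 per arm (168) with 36 per arm (216) for f=0.25.
2. State the sensitivity of the planned size: under a one-way ANOVA, 600 participants give 80% power for f of about 0.15, or about 0.16 with 510 after 15% loss. At f=0.1 power is about 43% and 37% respectively.
3. Qualify the power statements in Sample Size for Repeated Measures and Sample Size Justification so that they do not extend to f=0.1.
4. If the repeated-measures analysis is to be credited with more power, show that calculation with the assumed number of time points, the correlation of 0.3 and the attrition allowance.

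The cost is wording, plus a short calculation if item 4 is used. No extra participants are needed to make the text correct, but the stated sensitivity becomes less favourable. If the sponsor instead wishes to keep 80% power at f=0.1 under the ANOVA, the target becomes 215/0.85 = 252.9, that is 253 per arm or 1,518 recruited.
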